### 2.5. Procedures

Intervention group—Moderate-Intensity Interval Training (MIIT)

A supervised moderate-intensity interval training program will be applied using an upper-extremity cycle ergometer (Monark 881E Rehab Trainer, Monark, Vansbro, Sweden). The exercise program will be individualized by healthcare providers (physiotherapists and physicians) with more than five years of experience working with hip fracture patients. Additional external partners (physiotherapists) will be recruited for delivering the postoperative program. A commercially available athlete monitoring system app (Athlete Monitoring, Fitstats Inc., Moncton, NB, Canada) will be used for recording and documenting all training sessions’ features (intensity based on HR, duration, RPE, pain intensity and adverse events). The adherence rate will be calculated as the proportion of planned exercise sessions taken. Heart rate (HR) will be constantly recorded during each exercise session using an optical HR monitor (Polar OH1+, Polar Electro, Kempele, Finland). Oxygen saturation and blood pressure will also be assessed before and regularly during exercise. Pain intensity will be measured using a 20-point rating of perceived exertion scale (RPE) and will be considered as a limiting factor in maintaining sufficient pace and intensity in the exercise program.

The preoperative program will be performed in-hospital at the “Attikon” University Hospital. It will consist of 120 s of moderate-intensity exercise using an upper-extremity cycle ergometer and 120 s of passive rest for four cycles. The basic program will last about 16 min, not including the warm-up and cool-down. An additional 5 min in total is calculated for warm-up and recovery. The program will run twice a day. Exercise will be set at the half-seat position. The upper-extremity cycle ergometer will be set up on a rolling table, which will be placed over the bed in a comfortable position for the patient that allows a complete stroke without discomfort and prevents motion above the shoulders’ height. The adaptation and evaluation of the exercise intensity will be performed by modifying the external load (watts) based on the targeted internal load (moderate intensity: 64–76% predicted HRmax, 12–13 RPE). The revolutions per minute (rpm) will be set at 50 ± 10. Predicted HRmax will be estimated from the following formulae [34]:211—(0.64 × age in years) or
164—(0.7 × age in years), if taking beta-blocker

After each session, the lactate concentration of the capillary blood will be collected via a hand-held lactate analyzer (Lactate Scout 4, EKF Diagnostics, Leipzig, Germany), and the aim will be to maintain the capillary blood lactate concentration up to 2.0 mmol/L (±0.5).

The postoperative program will be performed initially in the hospital and at home after discharge. It will consist of 120 s of moderate-intensity exercise and 120 s of passive rest for eight cycles. The basic program will last about 30 min, not including warm-up and cool-down. An additional 5 min in total is calculated for warm-up and recovery. The program will be performed three times a week for eight weeks. The adaptation of the exercise intensity will be regulated by modifying the external load (watts) to keep the internal load of moderate intensity (64–76% HRmax, 12–13 in RPE). For the postoperative program, individuals will be allowed to follow the standard care, such as physical therapy sessions added to aerobic exercise. Standard care refers to postoperative rehabilitation. Such intervention will not be a part of our study’s protocol, and we will not intervene in patients’ decision to participate in physiotherapy sessions. These sessions will not be delivered by the research team, but it will be mentioned if they were conducted.

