#### Attention Control Group

The control group will participate in a program of memory and attention activities of very low intensity with upper extremity movements using an interactive platform (Kinesthetic Multi-Sensory Games, Kinems, Greece). To maintain equal attention time with the intervention group, the program will last 20 min. There will be a simultaneous recording of the HR, while the RPE scale will be evaluated at the end of each session. For the postoperative program, no intervention will be performed beyond the standard care, such as physical therapy sessions without aerobic exercise.

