### 2.6. Safety Considerations and Handling of Adverse Events

The inpatient and home exercise programs will be implemented and supervised by health professionals certified in first aid. Any intervention out of the hospital will begin after a cardiac clearance of the patient. For participating in the pre- and postoperative exercise program, approval by the attending orthopedic physician will be a prerequisite. During the initial assessment for planning and for any individualized modification to the planned exercise program to minimize potential adverse effects, the therapist will consider the following: current medical condition; medical history; comorbidities (e.g., diabetes and hypertension); medication (including dosage and time of administration); relevant clinical data (e.g., resting blood pressure and HR and oxygen saturation); instructions and cautions from other healthcare professionals; past and recent physical activity level time before the fracture and other factors that may affect exercise prescription (e.g., another injury).

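### Section 2.5 names the 20-point perceived-exertion scale as the pain measure, although the same scale at 12–13 is the effort target that sets the load

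*Protocol article*

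**What the plan says.** All references are to the protocol article.

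- Section 2.5, on pain: "Pain intensity will be measured using a 20-point rating of perceived exertion scale (RPE) and will be considered as a limiting factor" in keeping up pace and intensity.
- Section 2.5, on what the app stores for each session: "intensity based on HR, duration, RPE, pain intensity and adverse events". RPE and pain intensity are two items in that list.
- Section 2.5, preoperative program: the watts are changed "based on the targeted internal load (moderate intensity: 64–76% predicted HRmax, 12–13 RPE". The postoperative program repeats the target, again changing the watts "to keep the internal load of moderate intensity (64–76% HRmax, 12–13 in RPE".
- Section 2.5, on heart rate: predicted maximum is 211 − 0.64 × age, or "164—(0.7 × age in years), if taking beta-blocker".
- Attention Control Group: "the RPE scale will be evaluated at the end of each session", with no mention of pain.
- Section 2.6: at the initial assessment the therapist considers "medication (including dosage and time of administration" and "relevant clinical data (e.g., resting blood pressure and HR and oxygen saturation", among other things.

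No other session-level pain scale is named. The modified Harris Hip Score in 2.7.3 has a pain item, but it is an outcome taken at admission and at weeks 4, 8, 26 and 52.

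**The concern.** Pain and perceived exertion are different quantities, and in this program they drive different decisions. Pain may hold the load back even when effort is low. Exertion is steered towards 12–13 by raising or lowering the watts. Naming one instrument for both leaves a recorded number open to two readings.

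This matters because several people must read the number the same way. Section 2.5 has additional external physiotherapists recruited for the postoperative program, which moves to the patient's home after discharge. Section 2.4.3 makes intense subjective discomfort during exercise a ground for withdrawal, yet the only named session-level instrument for pain is an exertion scale. At stake are how the load is set session by session, how pain limits it, and how the delivered dose and tolerability are later described. No test of a primary outcome is at stake.

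**Working it through.** **1. The instrument.** The document states no figure to reproduce for this part, so the check is a comparison of the text.

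| Place in section 2.5 | What RPE is there |
|---|---|
| Pain sentence | the instrument for pain intensity |
| Preoperative target | a measure of internal load, 12–13 wanted |
| Postoperative target | the same, 12–13 wanted |
| App record | an item distinct from pain intensity |

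The last three rows, and the name of the scale, treat RPE as exertion. The first row assigns it to pain. Either two ratings on one scale are meant, or the pain scale is misnamed; the text does not settle which.

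**2. What a rating of 12–13 would lead to.**

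| What the patient is rating | Read as exertion | Read as pain |
|---|---|---|
| Effort, little pain | on target, keep the watts | possibly limiting, reduce the watts |
| Pain, low effort | on target, keep the watts | possibly limiting, reduce the watts |

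In the first row the pain reading is wrong and the patient may be under-dosed. In the second row the exertion reading is wrong and a limiting pain may pass as correct effort.

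**3. Heart rate as the other guide (secondary).** Inputs from section 2.5: band = 64–76% of predicted maximum; maximum = 164 − 0.7 × age on a beta-blocker, 211 − 0.64 × age otherwise. Eligible age is 65 and over (2.4.1). Resting heart rate is not given, so it is assumed over 60–80 bpm.

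Age 80 on a beta-blocker: 164 − 0.7 × 80 = 108. Floor 0.64 × 108 = 69.1; ceiling 0.76 × 108 = 82.1 bpm.
Age 80 without: 211 − 0.64 × 80 = 159.8. Floor 102.3; ceiling 121.4 bpm.

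Other ages on a beta-blocker: 65, 75.8–90.1; 75, 71.4–84.7; 90, 64.6–76.8 bpm.

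Age at which the beta-blocker floor equals rest = (164 − rest/0.64)/0.7:

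| Assumed resting rate (bpm) | Floor equals rest at age | Floor minus rest at age 80 (bpm) |
|---|---|---|
| 60 | 100.4 | +9.1 |
| 65 | 89.2 | +4.1 |
| 70 | 78.0 | −0.9 |
| 75 | 66.9 | −5.9 |
| 80 | 55.7 | −10.9 |

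At an assumed 80 bpm the ceiling also equals rest, at age (164 − 80/0.76)/0.7 = 83.9. Without a beta-blocker, the floor at age 80 is 22.3 to 42.3 bpm above rest over the same range, so heart rate does guide the load there.

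**The case against.** The strongest reply is that this is one awkward sentence. The scale's own name, its place inside the internal-load target and the separate app entries all show that RPE also means exertion. Two ratings are probably intended. That is right, and a reader who infers that the protocol defines RPE only as pain goes too far. It does not remove the fault, because the sentence that says how pain is measured still names an exertion scale and no other is offered for the sessions.

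A reader might also infer that the two uses push the load in opposite directions. They do not for a given number: a high rating lowers the load on either meaning, and a low one permits more. The difficulty is confined to what a middling rating such as 12–13 stands for.

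A third inference is that RPE becomes non-comparable between the arms. No load is set from RPE in the control group, pain is not an outcome in Table 1, and section 2.8.2 describes no between-arm comparison of either rating. No stated analysis would be biased.

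Safeguards exist as well. Sessions are supervised, heart rate is recorded throughout, oxygen saturation and blood pressure are checked regularly, and 2.6.2 gives grounds for stopping. Lactate is taken before and after each session (2.7.4), with an aim of up to 2.0 mmol/L (±0.5). These limit harm, but they do not say what the RPE number means.

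On beta-blockers, the reply is that the plan already has a dedicated formula and has therapists weigh medication and resting heart rate. Which target prevails in a conflict may be detail for the full protocol. Much of this stands, so the point is offered only as a conditional addition.

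**Conclusion.** The point holds as a mis-specified instrument in the current procedures: section 2.5 measures pain with an exertion scale that it also uses to set the load. It is minor in consequence and cheap to correct, and therefore worth considering. Sample size, both primary outcomes and the between-arm analysis are untouched.

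The wording covers every exercise session of the 58 intervention patients. Planned postoperative sessions are 3 × 8 = 24 per patient, or 58 × 24 = 1,392 in all, plus two a day before surgery. That is exposure to the wording, not a count of misread or misdosed sessions; the documents give no basis for such a count.

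The beta-blocker part is secondary. It rests wholly on an assumed resting heart rate and on an unstated number of users. At about 70 bpm or more, the floor lies at or below rest around age 80. At 60 bpm it stays above rest until about age 100. A reader might infer that heart rate is useless as a guide in all patients on a beta-blocker; the protocol's figures do not support that.

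**What to change.** In section 2.5, rate pain on its own scale, for example a 0–10 numeric rating, and let that rating act as the limiting factor. Keep RPE for exertion only. The app already has separate places for the two. The cost is a change to one sentence and one extra rating per session, with no extra visit, device or blood sample.

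Optionally, add a sentence for patients on a beta-blocker whose heart-rate band lies at or near their resting rate: exertion RPE 12–13 sets the load, and the heart-rate ceiling is left to the physician. Section 2.6.2 lists no upper heart-rate limit, so any such ceiling is a clinical decision, and no value is proposed here. Medication and resting heart rate are already considered under 2.6, so identifying these patients needs nothing new.

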#### Attention Control Group

The control group will participate in a program of memory and attention activities of very low intensity with upper extremity movements using an interactive platform (Kinesthetic Multi-Sensory Games, Kinems, Greece). To maintain equal attention time with the intervention group, the program will last 20 min. There will be a simultaneous recording of the HR, while the RPE scale will be evaluated at the end of each session. For the postoperative program, no intervention will be performed beyond the standard care, such as physical therapy sessions without aerobic exercise.

### 2.6. Safety Considerations and Handling of Adverse Events

The inpatient and home exercise programs will be implemented and supervised by health professionals certified in first aid. Any intervention out of the hospital will begin after a cardiac clearance of the patient. For participating in the pre- and postoperative exercise program, approval by the attending orthopedic physician will be a prerequisite. During the initial assessment for planning and for any individualized modification to the planned exercise program to minimize potential adverse effects, the therapist will consider the following: current medical condition; medical history; comorbidities (e.g., diabetes and hypertension); medication (including dosage and time of administration); relevant clinical data (e.g., resting blood pressure and HR and oxygen saturation); instructions and cautions from other healthcare professionals; past and recent physical activity level time before the fracture and other factors that may affect exercise prescription (e.g., another injury).

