## 2. Materials and Methods

### 2.1. Study Design

The study protocol has been prospectively registered in the open database for study protocols, ClinialTrials.gov (registration number: NCT05389800) [33]. The study received approval number 402/26-7-2021 from the Institutional Review Board of the “Attikon” University Hospital (1st Department of Orthopaedic Surgery, National and Kapodistrian University of Athens) 7 September 2021.

A parallel group, single-blinded, randomized controlled trial (RCT) will be conducted with two groups of hip fracture patients. The sample will be recruited from a tertiary University Hospital (1st Department of Orthopaedic Surgery, “Attikon” University Hospital, Athens, Greece). The randomization will be done at the time of admission of the patients to the emergency department (ED) and after their written informed consent form. The study protocol’s instructions will be described through an informed consent form in plain language, along with all the procedures the subjects will undergo and the risks and benefits of participation. Allocation concealment will be ensured by using sequentially numbered, opaque, sealed envelopes. The envelopes were created by a biostatistician, who will participate actively in neither the delivery of any intervention nor in the outcome measures assessment. For the preoperative program, 116 patients need to be recruited, who will be randomized with a ratio of 1:1 using the block randomization method (58 in the intervention group and 58 in the control group). Immediately after the surgery, the participants of each group will continue in the postoperative intervention program: the intervention group (IG) will continue with the exercise program three times a week for a total of 8 weeks, while the control group (CG) will not receive any intervention at any time point after surgery (Figure 1, graphic illustration).

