### 2.2. Implementation of the Study

#### 2.2.1. Getting Informed Consent

Participants will be informed of the purpose of the study, and their signed consent will be requested at the start of the study after it has been ensured that they meet the inclusion criteria and do not meet any of the exclusion criteria. Participation in the study is voluntary, and participants may discontinue participation at any time.

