#### 2.4.2. Exclusion Criteria

Pathological fractures (on the ground of malignant musculoskeletal tumor)Unable to implement the exercise program due to underlying pathology or disability in the upper extremitiesMore than one fractureUnderlying avascular necrosisSevere and unstable cardiovascular disease (e.g., congenital heart disease, severe uncontrolled hypertension (systolic blood pressure ≥180 mmHg or diastolic blood pressure ≥120 mmHg) or unstable angina)Neurological or other conditions that significantly impair function and independence (e.g., stages 3–5 Parkinson’s disease based on the Hoehn and Yahr scale, advanced multiple sclerosis or severe osteoarthritis of degenerative or rheumatic etiology)Severe metabolic bone disease (e.g., Paget’s disease, renal bone disease or osteomalacia), excluding osteoporosisAny aggressive end-of-life disease (e.g., end-stage cancer with an estimated survival expectancy of less than six months)Unable to understand the informed consent form and protocol instructionsRefusal to participate in the research

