#### 2.4.3. Withdrawal Criteria

Inability to participate in the inpatient program for more than two consecutive days (e.g., due to fever or early surgery within two days) or abstinence from more than 20% of the scheduled sessions in the postoperative programIntense subjective discomfort during exercise or development of other severe symptomatology or signs, as described in Section 2.4. Safety considerations and handling of adverse eventsPatient’s choice to drop out of the program

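### Several absolute contraindications to exercise are not named among the exclusions checked before randomisation, so patients who may not exercise can be randomised and then go untreated or be lost mainly from the exercise arm

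*Protocol article*

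**What the plan says.** All references are to the protocol article.

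- **Timing of allocation (Section 2.1).** "The randomization will be done at the time of admission of the patients to the emergency department (ED"), after written consent.
- **What is checked first (Section 2.2.1).** Consent is sought "after it has been ensured that they meet the inclusion criteria and do not meet any of the exclusion criteria". These are the Section 2.4 lists; Section 2.6 is not mentioned there.
- **Approval (Section 2.6).** "For participating in the pre- and postoperative exercise program, approval by the attending orthopedic physician will be a prerequisite". No time is given.
- **Cardiac clearance (Section 2.6).** "Any intervention out of the hospital will begin after a cardiac clearance of the patient".
- **Contraindications (Section 2.6.1).** A list headed as absolute. It includes renal failure, uncontrolled diabetes, retinopathy, interstitial lung disease, aortic stenosis, recent stroke and fever.
- **Withdrawal (Section 2.4.3).** "Inability to participate in the inpatient program for more than two consecutive days", or "abstinence from more than 20% of the scheduled sessions" in the postoperative programme.
- **Control arm.** Before surgery, very low intensity memory and attention games (the attention control group part of Section 2.5). After surgery, "the control group (CG) will not receive any intervention at any time point after surgery" (Section 2.1).

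**The concern.** Eligibility and permission to exercise are set by two lists that differ, and only the first is tied to a time before allocation. A patient can satisfy Section 2.4, be randomised, and then prove to be barred under Section 2.6. In the control arm nothing follows, because the contraindications and the approval are attached to a programme that controls do not receive. In the exercise arm there are two possible consequences:

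- The patient stays in the trial without the intervention, which dilutes the effect.
- The patient misses enough sessions to meet a withdrawal rule. If such patients are frailer than average, taking them out of one arm makes exercise look better than it is.

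There is also a patient-safety interest in having the two lists agree.

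**Working it through.** **1. Comparing the lists.** Unstable angina is the only condition named in both Section 2.4.2 and Section 2.6.1. The rest of Section 2.6.1 falls into three groups:

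- *Possibly covered by the open-ended cardiovascular exclusion:* decompensated heart failure, uncontrolled arrhythmia, high-grade block, left main disease, severe stenosis, recent infarction.
- *Covered only if the item on inability to carry out the exercise programme is read broadly:* renal failure, retinopathy, uncontrolled diabetes, severe neuropathy, interstitial lung disease. That item may refer only to the upper extremities, and it does not cite Section 2.6.1.
- *Able to arise after allocation:* fever, acute pulmonary embolism or deep-vein thrombosis.

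**2. Which withdrawal rule is one-sided.** The two-day rule concerns the inpatient programme. Controls have one too before surgery, so it can remove patients from either arm. The 20% rule concerns postoperative study sessions, which only the exercise arm has. Cardiac clearance for home exercise necessarily follows randomisation and also concerns only that arm.

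**3. The plan's own figure.** Section 2.8.1 gives 250 v 300 m, SD 75, α = 0.05, power 90%. With a two-sided test:

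n = 2 × (1.960 + 1.282)² × 75² / 50² = 47.3, so 48 per arm. Then 48 × 1.2 = 57.6, so 58 per arm and 116 in total. This reproduces.

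**4. Dilution (barred patients kept, untreated, no benefit).** The prevalence is an assumption: 5–10% of 58, or about 3–6 patients. The diluted effect is 50 × (1 − p). With 48 evaluable per arm, SE = 75 × √(2/48) = 15.31 m and power = Φ(effect/SE − 1.960).

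| Barred | Effect (m) | Power |
|---|---|---|
| 0% | 50 | Φ(1.306) = 90.4% |
| 5% | 47.5 | Φ(1.143) = 87.3% |
| 10% | 45 | Φ(0.979) = 83.6% |

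A t-test calculation gives 89.8%, 86.7% and 82.9%. The 3-day CAS is less exposed: with 52 evaluable per arm (58 less 10%), power goes from 97.7% to 94.4% at 10% barred.

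**5. One-arm removal.** Power changes little (89.7% at 5%, 88.9% at 10%). The bias is the larger issue. If being barred reflects a latent status correlated r with walking distance, removing the lowest fraction p from one arm shifts its mean by r × 75 × φ(z)/(1 − p), where z is the normal quantile for p. Both p and r are assumptions.

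| p | φ(z)/(1 − p) | r = 0.2 | r = 0.3 | r = 0.5 |
|---|---|---|---|---|
| 5% | 0.1031/0.95 = 0.1086 | 1.6 m | 2.4 m | 4.1 m |
| 10% | 0.1755/0.90 = 0.1950 | 2.9 m | 4.4 m | 7.3 m |

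At 10% removed, a shift of 4 m takes the two-sided type I error from 5% to about 5.7%, and a shift of 7.5 m to about 7.6%.

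**The case against.** The strongest reply has five parts.

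- **Timing is inferred.** A reader might infer that approval is sought only after allocation and only in the exercise arm. The article does not say so; it gives no time for approval before the preoperative programme. This part of the objection stands. What remains is that approval is not among the criteria stated to precede consent, and that cardiac clearance for home exercise must come later.
- **Not named is not the same as not excluded.** The cardiovascular exclusion is open-ended, and the item on inability to exercise can be read broadly. This stands in part: it narrows the gap, but it does not clearly cover the renal, ocular, metabolic and pulmonary items.
- **Withdrawal is not confined to one arm.** No passage says that a contraindicated patient is withdrawn as such, and the two-day inpatient rule can also remove controls. This stands. The one-sided route is clear only for the postoperative 20% rule.
- **Blood pressure.** It is tempting to say that the exclusion at "diastolic blood pressure ≥120 mmHg" contradicts the 105 mmHg figure in Section 2.6.2. One is an eligibility limit and the other a rule for pausing a session, so they do not contradict each other directly. How they fit together for a resting diastolic pressure between the two figures is unclear.
- **Size.** The 20% inflation in Section 2.8.1 already mentions comorbidities that force the programme to stop, so starting from 48 per arm may count some patients twice. This is fair for power: if all 58 per arm were evaluable, SE = 75 × √(2/58) = 13.93 m and power at 45 m would be Φ(45/13.93 − 1.960) = Φ(1.271), about 90%. Extra patients do not remove bias, however. The 7 m figure is the unfavourable end: it implies that barred patients walk about 37.5 × 0.1755/0.10 = 66 m less than the overall mean.

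**Conclusion.** The concern holds as a mismatch between what is checked before allocation and what is required to exercise. As written, patients with a listed absolute contraindication can be randomised, and the loss is most clearly one-sided after surgery. No stated number is wrong, and the sample size of 116 reproduces.

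The size is modest and conditional. With 5–10% barred, either power for the six-minute walk test falls to about 83–87% (kept untreated, 48 evaluable per arm) or a spurious gain of roughly 2–7 m appears (removed from one arm, r = 0.2–0.5). The documents give neither the prevalence nor the correlation.

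The documents do not establish that approval always follows allocation, that no contraindication is covered by the exclusions, or that the blood-pressure figures conflict outright. This is a cheap improvement worth making, not a fatal defect.

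**What to change.** 1. Reconcile Section 2.4.2 with Section 2.6.1, with a cross-reference. Which conditions bar exercise is for the clinical team to decide.
2. State that the reconciled list and the physician's approval for the preoperative programme are completed for every candidate before the envelope is opened, using what is known at admission.
3. State that patients who become contraindicated, or fail approval or clearance, after randomisation remain in follow-up and are analysed as randomised. Screening at admission cannot prevent these cases.
4. Ask the clinical team to clarify how the diastolic figures in Sections 2.4.2 and 2.6.2 apply to a patient whose resting value lies between them.

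The cost is protocol wording and a checklist moved earlier. The target of 116 does not change. The downside is that a few more candidates are screened out. Conditions not known at admission will still be missed, and the article does not say which of them are normally known in the emergency department.
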